## Abstract

Background and aim: The use of mHealth, especially short-message text (SMS), has proven to be an effective intervention in promoting behavioral health outcomes in populations across different contexts and settings. While MomConnect, an mHealth technological device designed to enhance maternal and child health services in South Africa, offers various health-related contents aimed at improving maternal outcomes for pregnant and postpartum women, it currently lacks information on prenatal physical activity. However, physical activity and exercise during pregnancy is safe and beneficial for both the mother and the baby. This article outlines the protocol for designing and developing a prenatal physical activity and exercise text messaging content for the MomConnect device. To achieve this, the protocol aims to elucidate the preferences of prenatal physical activity and exercise text messages and ascertain the preferred amount of SMS messaging to inform the design of an intervention for the incorporation of prenatal physical activity and exercise text messages into the MomConnect device in South Africa. Methods: We will apply a user-centred design approach conducted in three phases. First, a scoping literature review and interviews with pregnant women will be conducted to inform the formative stage for developing a desirable prototype SMS. Secondly, healthcare providers and pregnant women will be interviewed to collate data on the preferred SMS. Lastly, a cross-sectional survey will be conducted to determine the preferred quantity of SMS messaging to be incorporated in the MomConnect device. Expected outcomes: A preferred or desirable prenatal physical activity and exercise SMS text message will inform the design of SMS text messages to be incorporated into the content of the MomConnect device to promote prenatal physical activity and exercise participation among women in the Eastern Cape Province. This study will develop a tailored mHealth intervention to improve prenatal physical activity participation and health behaviors among pregnant women in South Africa.

## 1. Introduction

Pregnancy is an important phase in any woman’s life marked that is with unique physiological changes, which can influence lifestyle behaviors, such as physical activity and exercise. Providing pregnant women with adequate maternal health counseling, which includes physical activity and exercise, is crucial for both the mother and the baby. Research has demonstrated that engaging in physical activity during pregnancy improves maternal outcomes. Thus, healthcare providers should advise pregnant women without any medical problems to exercise regularly. Research shows that frequent activity during pregnancy reduces the incidence of prenatal hypertension, diabetes, obesity, pre-eclampsia, and musculoskeletal lower back pain and shortens labor [1,2,3,4]. Also, prenatal physical activity enhances mental health and quality and decreases the risk of postpartum depression [5,6]; improves breastfeeding outcomes [7]; decreases neonatal complications; and improves the fetal nervous system of the child [8,9,10]. Inactivity during pregnancy could negate the benefits of exercise. However, individuals in both developing [11,12,13,14] and developed [15] countries exhibit significantly lower levels of physical activity compared to those in other countries, a trend that is associated with increased sedentary behavior [16,17]. Similarly, in South Africa, earlier studies have reported low prenatal physical activity [18,19]. This highlights the importance of advocacy and counseling to encourage physical activity and exercise during pregnancy in order to avoid sedentary behaviors.

There are studies in the literature on the reasons for inactivity during pregnancy. These include a lack of motivation, a lack of knowledge, and safety concerns [20,21,22,23,24]. Raising awareness about the importance of physical activity during pregnancy might improve women’s attitudes toward prenatal physical activity. As such, exploring feasible interventional strategies, such as digital technology (mHealth), to promote the uptake of physical activity and exercise during pregnancy and achieve desirable maternal and fetal health outcomes is crucial.

Digital behavioral intervention through text messaging could potentially aid in the promotion of prenatal physical activity and confer multiple advantages. Mobile health (mHealth) interventions help recognize the benefits and opportunities of exercise, create attainable goals, and promote accountability [25], and they are widely accessible and cheap to use [26]. Several studies have shown the efficacy of mHealth interventions in promoting PA in varying populations [25,27,28,29]. Notably, motivational text messaging is potentially a positive adjutant to an mHealth PA intervention [30,31]. Nevertheless, the impact of motivational messages on physical activity behavior appears insignificant and declines over time [30]. Therefore, personalizing and adapting physical activity text messages to participants’ contextual characteristics could potentially ensure the sustainability of a desired change in physical activity behavior.

However, scant information exists on the use of text messages to encourage physical activity and exercise during pregnancy in South Africa. Notably, pregnant women and other stakeholders have advocated for the incorporation of physical activity content in the existing mHealth technology (MomConnect) in South Africa to promote prenatal activity participation [32]. In addition, a study on mHealth interventions to improve antenatal care seeking and health behavioral determinants during pregnancy among adolescent girls and young women in South Africa highlights that the participants expressed a desire for the inclusion of exercise activity in the content of MomConnect [33].

MomConnect is one of the popular, phone-based technological maternal initiative health programs designed by the National Department of Health in South Africa to support and improve maternal health and child health services [34,35,36,37]. The program registers expectant mothers into a national pregnancy registry, sends weekly informational texts, and creates an interactive support desk [34,35,36]. MomConnect sends targeted maternal and child health information to mothers during pregnancy and up to one year postpartum [35]. The MomConnect health promotional messages are freely available to users (pregnant women) in all of the 11 South African official languages. The health messages cover topics such as antenatal care, accessing care during labor, diet and nutrition, managing non-pregnancy-related infections, managing hypertension, caring for newborns, breastfeeding, and vaccination. The absence of MomConnect content regarding physical activity and exercise engagement during pregnancy highlights the importance of this study. This protocol is designed to conduct a feasibility study to provide the groundwork for the designing and development of acceptable prenatal physical activity text messages to aid the facilitation of physical activity among pregnant women in the context of the Eastern Cape Province, South Africa, where physical activity participation is reportedly low due to varying factors [18,32]. It is probable that expectant women and mothers who receive prenatal physical-activity-related information via ‘SMSs’ linked to the MomConnect device may be encouraged to engage in physical activity during pregnancy.

### 1.1. Objectives

This protocol paper aims to conduct a literature review on the preferred and acceptable SMS prenatal physical activity among pregnant women, develop and design a prototype prenatal physical activity text message for infusion into the MomConnect device, and determine the frequency and timing of the SMS test messages.

### 1.2. Expected Outcome

The planned study’s findings will guide the design and implementation of a digital prenatal physical activity program that uses SMS text messages incorporated into the MomConnect health device to improve physical activity behavior during pregnancy.

## 2. Methodology

### 2.1. Research Design

Applying the methodological approach used by Huberty et al. [38], this study will employ a user-centred approach to gather qualitative and quantitative data from both pregnant and non-pregnant women with the goal of designing a prototype prenatal physical activity SMS that can be integrated into the MomConnect technological device to encourage active physical activity during pregnancy. The findings from the qualitative data will inform the design of Phase III, which is the quantitative survey study. Table 1 provides a methodological summary of the study protocol, highlighting each phase of the study.

### 2.2. Phase 1: Interviews and Prototype Development

This phase will employ qualitative research methods, including interviews and literature reviews, to explore the needs and opinions of pregnant women regarding their preferred and acceptable prenatal exercise routines. We will conduct interviews with expectant women who participate in moderate-intensity physical activity, as recommended by various bodies and organizations (The Royal Australian New Zealand College of Obstetricians and Gynaecologists [39,40,41,42]), to identify potential themes relating to barriers and strategies for the text message prototypes [38]. Women visiting antenatal clinics will be invited to participate in the study. Active pregnant women and women who have been previously pregnant, 18 years or older, able to speak English and isiXhosa, and engaged in at least 30 min of moderate activity five days a week (more than 150 min) in the preceding week (self-reported) [38] will be purposively selected to participate in the study.

Participants who agree to participate in the study will be requested to confirm their eligibility in person before an interview is scheduled. With permission from the selected health facility managers, the participants will be interviewed in a quiet designated place provided in each of the health facilities before antenatal sessions. All interviews will be recorded and transcribed verbatim. The interviews will take 30 to 40 min. Interviews will continue until saturation is achieved (no new emerging facts or information) [43,44]. The data collection tool will be developed by the researchers.

Pregnant women will be interviewed to uncover the underlying cause of their activeness, anxieties, and strategies to increase their prenatal activity level [38]. We will analyze the interviews using a case study technique, which allows for multiple analyses of bound systems (cases) [38]. This technique involves collecting detailed data through interviews, reports, case descriptions, and case-based themes [45,46]. The coders will encode and recode the data based on the themes identified. The coders will create themes based on the objectives of the study and then use them to create categories for text message prototypes. Interviewers will ask the following questions:Do you think that exercise is beneficial to both mother and child and why?Do you think that prenatal physical activity and exercise during pregnancy reduce the risk of preterm labor, anxiety, enhance oxygen supply for the baby, and enable easy labor, and why?What strategies do you think can best increase your prenatal physical activity participation?

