## Figures and Tables

**Table 1 mps-08-00026-t001:** Methodological summary of the protocol stratified by study phases.

Phase	Objective	Design	Population and Sample	Analysis	Outcome Measure
I	Conduct a scoping review on prenatal physical activity test SMS preferences and acceptability among pregnant women	Systematic Reviews and Meta-analyses (PRISMA) methodology for scoping review	Published articles meeting the selection criteria	Narrative synthesis	Evidence based on MomConnect’s effectiveness, efficiency, and acceptability as a facilitator of health behavioral outcomes
	Conduct formative research to determine a prenatal physical activity test SMS acceptable to pregnant women	Qualitative (interviews)	Pregnant women (purposive)	Case study approach	Content case-based themes of text message prototype development
II	Develop prototype prenatal physical activity text messages	Qualitative (interviews)	Prenatal care health providers (physicians, nurses/midwives) and pregnant women	Thematic content analysis	Feasibility and appropriateness of the prenatal physical activity test messages
III	Determine the acceptable dose of prenatal physical activity test messages	Quantitative (cross-sectional survey)	Pregnant and non-pregnant women	Descriptive analysis (frequency and percentages)	Acceptability and preferred prenatal physical activity SMSs desirable for inclusion in MomConnect device

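### The three printed Phase 1 interview questions directly cover only one of the stated interview aims (strategies), and two of the three are suggestive and multi-part

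*Protocol article*

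**What the plan says.** Section 2.2 states the purpose of the Phase 1 interviews twice. Near its start they are "to identify potential themes relating to barriers and strategies for the text message prototypes". Further on, women are interviewed "to uncover the underlying cause of their activeness, anxieties, and strategies to increase their prenatal activity level". Table 1 gives the interview part of Phase I another objective: "Conduct formative research to determine a prenatal physical activity test SMS acceptable to pregnant women".

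The section then lists three questions that interviewers will put:

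1. "Do you think that exercise is beneficial to both mother and child and why"
2. "Do you think that prenatal physical activity and exercise during pregnancy reduce the risk of preterm labor, anxiety, enhance oxygen supply for the baby", to which the same sentence adds easy labor and an open 'why'
3. "What strategies do you think can best increase your prenatal physical activity participation"

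Four other statements bear on how to read this list:

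- The women are chosen because they already exercise at the recommended level (section 2.2).
- Interviews last 30 to 40 minutes and are recorded and transcribed (section 2.2).
- The data collection tool has yet to be developed (section 2.2).
- Coders form themes from the study objectives and turn them into message categories (section 2.2). Section 2.3 then has prototypes written for each of those categories.

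**The concern.** A formative interview can only reliably yield themes on topics that it raises. Here the aims and the printed questions stand in the same section and do not match. Most of what the interviews are meant to find out has no question behind it. Two of the three questions instead put benefits of exercise to the woman and ask whether she agrees.

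Two consequences follow if the list is used as printed. First, talk about benefits will be prompted in every interview, in the terms the interviewer supplied, while talk about barriers and worries depends on a woman bringing it up. Second, the imbalance carries forward, because the Phase 1 categories decide which messages get written. The Introduction names lack of motivation, lack of knowledge and safety concerns as reasons for inactivity, yet no listed question invites a woman to mention harm or fear. The Discussion itself notes that frequent irrelevant messages may lower activity, so the relevance of the categories matters to the protocol's own argument.

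**Working it through.** No formula applies and the plan gives no figure to reproduce. The check sets each stated aim beside each printed question, and then looks at the form of each question.

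**Distinct aims.** The first statement in section 2.2 gives barriers and strategies. The second gives cause of activeness, anxieties and strategies. Strategies occurs in both, so the distinct aims number 2 + 3 − 1 = 4. Table 1 adds an acceptable SMS, which is treated separately below.

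**Aim against question.**

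| Stated aim | Question 1 (benefit to mother and child) | Question 2 (four benefits) | Question 3 (strategies) |
|---|---|---|---|
| Barriers | no | no | no |
| The woman's own anxieties | no | no: anxiety appears only as something exercise reduces | no |
| Cause of her activeness | not directly: the 'why' asks why exercise is beneficial | not directly, for the same reason | no |
| Strategies | no | no | yes |

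So 1 of 4 aims has a direct question and 3 of 4 have none. A woman may explain a belief in benefit by saying why she exercises, so the 'why' in the first two questions could touch on activeness. That would be incidental.

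**Form of each question.**

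- Question 1 puts benefit in the stem and joins two subjects, mother and child. It does not mention harm.
- Question 2 puts four claims in one stem: less preterm labor, less anxiety, better oxygen supply and easier labor. A woman who accepts some and doubts others must separate them herself.
- Question 3 is open, has one topic and is not leading.

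Two of three questions are therefore suggestive and multi-part, and one is sound.

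**SMS.** None of the three questions mentions text messages, although the Table 1 objective is an acceptable SMS. The outcome that Table 1 gives for the same interviews is narrower: themes that feed prototype development. Section 2.3 asks about the messages in Phase 2, once there are prototypes to show. The gap here lies mainly in the wording of the Table 1 objective.

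**Path to the messages.** Interview answers become themes, themes become categories, and prototypes are written per category. The four Phase 2 questions ask for a view of the messages, whether they would help, how to improve them and which is preferred. They ask for reactions to messages already drafted and do not ask about barriers.

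**The case against.** The strongest reply is that the printed list is not shown to be the whole instrument. The tool is still to be developed, section 2.8 mentions an interview guide that is not reproduced, and a journal article may well condense it. Three questions in 30 to 40 minutes leave room for probing. This stands in part: one cannot conclude that the questions are fixed or that barriers will never be raised. But section 2.2 commits interviewers to these questions without calling them examples, and it describes no probes. The first two are poorly framed whether or not others follow. The point is a mismatch between two things the article chose to print, not a detail left out.

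A reader might also infer that Phase 1 cannot produce usable message categories. The documents do not support that. The third question can yield strategy categories, the first two can yield categories of belief about benefits, and the Abstract says that a scoping review also informs the prototype. According to Table 1, however, that review concerns SMS preferences and acceptability and MomConnect's performance. Neither entry covers these women's barriers, anxieties or reasons for being active.

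Nor should the second question be read as a yes/no item that squeezes four beliefs into one recorded answer. It ends with an open 'why', the reply is transcribed, and section 2.7 plans thematic analysis, not a tally. A woman can agree with one claim and reject another. The first question likewise suggests benefit without presupposing it, since she can say no.

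Finally, Phase 2 interviews include sedentary women and ask for improvements, and the pilot in section 2.5 can restructure content. These are real chances of correction. They come after the categories are set, and neither asks about barriers directly.

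**Conclusion.** The point holds as a mismatch between aims and questions, together with weak framing of two questions. Of the four interview aims in section 2.2, one (strategies) has a direct printed question; barriers, the woman's own anxieties and her reasons for being active have none. Two of the three questions suggest benefits and combine several matters, the second joining four. The likely effect is a set of categories weighted towards suggested benefits, with barriers and anxieties appearing only by chance.

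This rests on two assumptions. The first is that the guide follows the printed list; a fuller guide with neutral questions on the missing aims would remove most of the concern. The second is that women chosen for being active will tend to agree with benefits put to them. That is plausible, but the documents give no evidence for it, and the gap in coverage does not depend on it. The size of any tilt cannot be estimated. The change should be made before the first interview, because questions not asked then are hard to recover later.

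**What to change.** While the tool is being developed:

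- Replace the first question with a neutral open item, for example: *What, if anything, do you see as the benefits or harms of exercise in pregnancy?*
- Add one open question each on what made the woman active, what hinders her and what worries her.
- Keep the third question as it is.
- If the specific beliefs in the second question are wanted, ask each one separately and after the open items.
- Either add an open item on what she would or would not want in a text message about exercise, or reword the Table 1 Phase I interview objective so that SMS acceptability is left to Phase 2.
- If the three printed questions are meant only as examples, say so in section 2.2.

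The cost is a small change to the interview guide and possibly a notification to the ethics committee, which has approved the protocol. The added questions should be accommodated within the planned 30 to 40 minutes.

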### 2.3. Phase 2: Assessment of Prototype Prenatal Messaging

During Phase 2, prototype text messages will be developed for each of the categories identified in Phase 1. Prototype text messages will provide mobile-friendly access to the MomConnect network and will be limited to 150 characters or fewer. Next, we will conduct interviews to ascertain the perceived preference and acceptability of the prenatal physical SMSs within the context of the setting [38]. A convenient sample of prenatal care providers, including physicians, nurses/midwives, and sedentary pregnant women who do not meet the recommended 150 min of moderate-intensity physical activity per week, will be interviewed. Participants in the interviews will be recruited in health facilities. Participants must be (i) a doctor, nurse/midwife, or pregnant patient at antenatal health facility, (ii) able to speak English and isiXhosa, and (iii) at least 18 years old to be eligible for the study. In-person interviews in a quiet designated place provided in each of the health facilities by the facility manager. Participants will be provided with three prototype text messages for each developing category. The interviewer will present the text messages to the participants and then ask the following questions [38]:Would you be able to share your perspective on the text messages?Do you believe these messages would support women in increasing their physical activity?What improvements do you believe could enhance the messages?Which SMS message, out of all of them, would you prefer, and why?

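### The Phase 2 preference question, read literally, takes one favourite across all categories and so does not reliably elicit a preference among the three prototypes in each category

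*Protocol article*

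**What the plan says.** In section 2.2 the Phase 1 coders derive themes and then "use them to create categories for text message prototypes". Section 2.3 continues that structure: "prototype text messages will be developed for each of the categories identified in Phase 1", and "Participants will be provided with three prototype text messages for each developing category". The procedure is given in one sentence: "The interviewer will present the text messages to the participants and then ask the following questions". Four questions follow. The first asks for views on the messages, the second whether they would help women become more active, and the third is "What improvements do you believe could enhance the messages". The fourth, and the only comparative one, is "Which SMS message, out of all of them, would you prefer, and why".

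The stated purpose is: "Next, we will conduct interviews to ascertain the perceived preference and acceptability of the prenatal physical SMSs within the context of the setting". Table 1 gives the Phase II outcome as "Feasibility and appropriateness of the prenatal physical activity test messages". Section 2.7 assigns thematic content analysis to Phases I and II and gives no counting or ranking rule. The article states neither the number of categories nor the number of Phase 2 interviewees. It also does not say whether the four questions are put once at the end or after each category's set.

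**The concern.** The stimuli are arranged as alternatives within a category, but the question asks for a single choice across categories. A woman who cares most about labour will tend to choose a message about labour, whichever of its three wordings is best. Her answer therefore reflects topic and wording together, and the two cannot be separated unless her reasons happen to do so. For every other category she is not asked to choose among the three alternatives.

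This matters because no later step described in the article asks participants to choose between messages. The Phase 3 survey items in section 2.4 are frequency and time of day. The pilot in section 2.5 covers understanding of the content, timing and frequency. Yet the Phase III row of Table 1 expects preferred messages, in the plural, for inclusion in MomConnect. If Phase 2 gives little information for some categories, the choice among their three wordings rests more on the researchers' judgement than a user-centred design intends.

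**Working it through.** The plan has no figure of its own to reproduce here, so the check is a reading of the text plus an illustrative count.

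**Inputs**
- Messages per category: 3 (section 2.3).
- Number of categories, K: not stated; assumed.
- Number of interviewees, n: not stated; assumed. It includes providers as well as pregnant women.
- Share of choices going to each category: assumed equal (1/K) at first, then unequal.

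**Formulas**
- Messages shown per respondent: 3K.
- Choices per category with one overall question: n/K on average. With one question per category: n. The ratio is K whatever n is.
- Probability that a given category receives no choice under the overall question: (1 − 1/K)^n with equal shares, or (1 − p)^n for a category with share p.

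**Results with equal shares**

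| K | Messages shown | n | Choices per category, one overall question | Choices per category, asked per category | P(a given category gets none) |
|---|---|---|---|---|---|
| 3 | 9 | 10 | 3.3 | 10 | (2/3)^10 = 0.017 |
| 3 | 9 | 20 | 6.7 | 20 | (2/3)^20 = 0.0003 |
| 5 | 15 | 10 | 2.0 | 10 | (4/5)^10 = 0.107 |
| 5 | 15 | 20 | 4.0 | 20 | (4/5)^20 = 0.012 |
| 8 | 24 | 10 | 1.25 | 10 | (7/8)^10 = 0.263 |
| 8 | 24 | 20 | 2.5 | 20 | (7/8)^20 = 0.069 |

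The choices within a category are then divided among three wordings. At K = 5 and n = 20 that is 4/3 ≈ 1.3 per message, against 20/3 ≈ 6.7 if asked per category.

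**Results with unequal shares**

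A category that attracts 5% of choices receives none with probability 0.95^10 = 0.60 at n = 10, 0.95^20 = 0.36 at n = 20, and 0.95^30 = 0.21 at n = 30.

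**What the count shows**

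Only the factor K follows from the layout itself, and only under the literal reading. With few, equally popular categories an empty category is unlikely. Sparse or empty categories become a practical problem when there are many categories, few interviews or uneven topic appeal.

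**The case against.** A reader might infer that Phase 2 cannot select a preferred message within a category at all. The document does not support that, for four reasons.

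1. The text does not say whether the four questions are asked once or after each category. If they are repeated, the fourth question refers to the three messages just shown and already does what is wanted. A separate interview guide, mentioned in section 2.8 but not shown, may settle this.
2. Choosing one message per category is nowhere a stated objective. It is inferred from the layout of three alternatives per category. The stated aim is preference and acceptability in general, and the abstract's expected outcome speaks of a preferred message in the singular, which an overall favourite would fit.
3. The phase is qualitative. The preference question also asks for reasons, the other three questions are open to comments on every message, and the analysis is thematic, not a tally. Pilot feedback will also be used to restructure content.
4. Pooled over interviewees, choices can fall in several categories and still say something about wording within each.

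All four stand as limits on the point, but they do not remove it. The concern is with printed question wording, not with an omitted detail. The other questions refer to the messages as a set, which makes the whole-set reading the natural one. Open comments may include comparisons but do not ensure one in each category. If repetition by category is intended, the same edit makes it explicit.

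**Conclusion.** The point holds in a limited form. As worded, the question does not reliably elicit a preference within each category. Under the literal reading, each respondent gives one choice where a per-category question would give K, and that choice mixes topic with wording. The information on wording is thinner and uneven, not absent. The counts rest on assumed values of K, n and the spread of choices. It would go too far to say that the wording defeats the user-centred aim, or that the researchers would necessarily choose the messages for the remaining categories. Severity is minor and confidence moderate, because repetition by category is possible. It is best treated as a cheap improvement.

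**What to change.** In section 2.3 and in the interview guide, put the preference question after each category's three messages, for example: *Of these three, which do you prefer, or none, and why?* Rotate the order of the three between participants so that position does not drive the choice. Keep one final question across categories, so that the overall favourite and the importance of topics are still recorded, separately from wording.

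The cost is a few more minutes per interview, growing with the number of categories. No extra participants are needed, and the thematic analysis can stay as planned.
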